### Variables assessments and definition

Upon study entry, each participant will have the following lab tests and imaging study:MELD score ≤ 15 (regardless of etiology) based on INR, total bilirubin, serum creatinine of latest test results from the most recent visit within six months of entry or at entryChild–Pugh score grade A (optional, if available)APRI > 0.7 in patient with anti-HCV positive based on anti-HCV (no time limit), AST, alanine aminotransferase (ALT), and platelet countFib-4 index ≥ 1 in patients who are hepatitis B surface antigen (HBsAg) positive or those with NAFLD based on HBsAg, AST, ALT, platelet count, and ageFibroscan kPa (HBV etiology is kPa ≥ 9, for HCV kPa ≥ 9, and for NAFLD kPa ≥ 8)Other variables from case report form (CRF): “Yes” vs. “No” for dichotomous variableDynamic contrast-enhanced MRI to rule out HCCGALAD score based on Gender, Age, AFP, AFP-L3, and PIVKA-II (DCP) of latest test results from the most recent visit within six months of entry.

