### Screening

Before or during the first visit, patients with chronic liver diseases, including advanced fibrosis/cirrhosis identified by ICD-10 from participating clinical sites, will be screened.

The screening criteria are MELD ≤ 15, non-invasive indices, and finally confirmed by Fibroscan or ARFI elastography results to further select those with fibrosis score F3 or higher from the 10 clinical centers’ databases in this Study Cohort Database (Fig. 1 & 3). All patients will be required to have a negative dynamic contrast-enhanced MRI upon study enrollment to rule out HCC before the study enrollment. Only MRI nearest to the time of GALAD score or abdominal ultrasound (US) and or AFP evaluation will be included in the analysis. If patients have a history of metal in their heads or eyes, they will need an x-ray of their skull to find out if the MRI is safe for them.

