### Schedule of activities

Data will be collected during screening (initial visit) and at semi-annual intervals thereafter (a maximum of ten visits). Schedule of activities (Table 1) displays the data collection schedule for screening and follow-up.

**Table 1 Tab1:** Schedule of activities

Procedures	Screening/baseline (Visit 1)	Study Visit 2	Study Visit 3	Study Visit 4	Study Visit 5	Study Visit 6	Study Visit 7	Study Visit 8	Study Visit 9	Final Study Visit 10
Informed consent	X									
Demographics	X									
Home address/Phone number	X	X	X	X	X	X	X	X	X	X
Medical history	X	X	X	X	X	X	X	X	X	X
Collect and archive serum (15 mL blood, 50 mL urine)	X	X	X	X	X	X	X	X	X	X
Concomitant medication review	X	X	X	X	X	X	X	X	X	X
Physical exam (including height and weight)	X	X	X	X	X	X	X	X	X	X
Vital signs	X	X	X	X	X	X	X	X	X	X
Height	X									
Weight	X	X	X	X	X	X	X	X	X	X
Waist circumference	X	X	X	X	X	X	X	X	X	X
Performance status	X	X	X	X	X	X	X	X	X	X
Handgrip strength measurements	X	X	X	X	X	X	X	X	X	X
Hematology	X	X	X	X	X	X	X	X	X	X
Serum chemistry	X	X	X	X	X	X	X	X	X	X
Adverse event review and evaluation		X	X	X	X	X	X	X	X	X
Radiologic/Imaging assessment (Abdominal Ultrasound and/or cross section imaging if triggered)	X	X	X	X	X	X	X	X	X	X
Dynamic contrast-enhanced CT or MRI	X		X		X		X			X
Fibroscan	X									X
Complete Case Report Forms (CRFs) that have clinical data and events	X	X	X	X	X	X	X	X	X	X

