### GALAD score

This study is considered a prospective observational cohort study. GALAD score, comprising Gender, Age, AFP-L3, AFP, and DCP, is an add-on test to the routine HCC surveillance care with the provisions of abdominal US and AFP every six months.

Japanese investigators have, for several decades, combined AFP with two additional markers, DCP and AFP-L3, for diagnosis and surveillance. DCP, also known as Protein Induced by Vitamin K Absence or Antagonist-II (PIVKA-II) is an immature form of prothrombin [12, 13]. Elevated DCP values (≥ 7.5 ng/ml) are associated with a fivefold increased risk of developing HCC, and on this basis, DCP has received USFDA approval for risk assessment. AFP-L3, a glycoprotein normally produced by the fetal liver, is one of three AFP glycoforms that can be separated based on their lectin binding characteristics, most readily with LCA. An increase in AFP-L3 appears more specific for HCC than total AFP in adults. It is usually presented as a percentage of the total AFP with a reference range of < 10%.

GALAD formally combines these three serum biomarkers together with age and gender to produce an algorithm with better performance than its individual constituents. The GALAD model is of the form: Z = -10.08 + 0.09 × age + 1.67 × sex + 2.34 log (AFP) + 0.04 × AFP-l3 + 1.33 × log (DCP). Where sex = 1 for males, 0 for females.

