## Discussion

Assays of AFP, AFP-L3%, and/or DCP have been available for clinical use in a few medical centers in Vietnam over the past five years [14]. Locally, the main indication for the use of the assay is to aid in the risk stratification for HCC in the cases of hepatic nodules with atypical features on cross-sectional imaging for HCC diagnosis, such as without arterial phase hyperenhancement or without delayed phase washout appearance [14]. Other indication, in Vietnam at least, is when AFP has risen upper limits of normal (locally > 9 ng/mL) [14], which often occurs in advanced HCC. There are no consensus national practice guidelines for the use of biomarkers [14]. Similar to Vietnam, GALAD score uptake in Saudi Arabia has not been widely used in clinical practice. Reasons for this include the lack of validated prospective data on GALAD score [6].

Taken together, the combined GALAD score has not been validated and thus utilized systematically for HCC surveillance in Vietnam or Saudi Arabia. Additionally, there is a lack of wide and uniform uptake of GALAD in clinical practice in Vietnam and Saudi Arabia, and there is a need for high-quality research on the use of the GALAD for HCC surveillance. The present work will attempt to fill this evidence gap by evaluating the performance of the GALAD score in early detection of liver cancer. Furthermore, by leveraging the prospective cohort, we will establish a biorepository of longitudinally collected biospecimens from patients with advanced fibrosis or cirrhosis to be used as a reference set for future research in the two countries.

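### The entry GALAD score may be built on marker results up to six months old, so it can precede the enrolment MRI by about 26 weeks

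*Protocol article*

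**What the plan says.** The list in Variables assessments and definition opens with "Upon study entry, each participant will have the following lab tests and imaging study". Its GALAD item then takes the markers, AFP included, from earlier records: "AFP-L3, and PIVKA-II (DCP) of latest test results from the most recent visit within six months of entry". The MELD item has nearly the same wording but adds entry itself as an alternative source.

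On the reference side, the Screening section states "All patients will be required to have a negative dynamic contrast-enhanced MRI upon study enrollment to rule out HCC before the study enrollment". The pairing rule there is "Only MRI nearest to the time of GALAD score or abdominal ultrasound (US) and or AFP evaluation will be included in the analysis", with no maximum interval.

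On the supply of markers:
- Eligibility requires only an AFP result before entry, within 180 days.
- The GALAD score section says that GALAD "is an add-on test to the routine HCC surveillance care", routine care being ultrasound and AFP.
- The Discussion says that the assays "have been available for clinical use in a few medical centers in Vietnam". It gives the main local uses as nodules with atypical imaging and AFP above the local upper limit. For Saudi Arabia it says only that GALAD is not in wide use.
- Blood is drawn at Visit 1; the row in Table 1 reads "Collect and archive serum (15 mL blood, 50 mL urine".

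**The concern.** The Background presents the study's novelty as applying GALAD in real time, with diagnostic work-up following the result. An entry score built on results from months earlier departs from that for the first value in each participant's series.

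Two things are at stake. First, the score and the enrolment MRI that it is paired with may describe the liver at different times. Second, where older AFP-L3 and DCP results exist in Vietnam, they may exist because a clinician was already suspicious. A baseline that mixes such results with fresh ones would not be a uniform sample of the cohort. Two sites could both follow the rule and still produce baselines that are not comparable.

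**Working it through.** The plan gives no figure to reproduce here. The check is a comparison of the stated timings, plus a small calculation from the printed GALAD formula.

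**1. Does another section override the rule?** The enrolment laboratory list names neither AFP-L3 nor DCP. Table 1 has no row for GALAD, AFP-L3 or DCP, and its Visit 1 blood row describes collection and archiving. The data collection section names AFP only. A condensed article may leave assay schedules to the full protocol, so these gaps are not a fault in themselves. They do mean that the GALAD line is the only rule in this document on where the entry markers come from.

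**2. Gap to the enrolment MRI.** The oldest permitted result is six months old, about 26 weeks. The MRI is done at enrolment, so the gap can reach about 26 weeks. By comparison, the Figure 3 caption lets screening and enrolment procedures spread over up to 30 days: 30 / 7 = 4.3 weeks. The nearest-MRI rule does not limit the gap, because it sets no maximum.

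**3. Gap to the next score.** Follow-up visits are 22 to 26 weeks apart. In the worst case the first two scores are 26 + 26 = 52 weeks apart, about twice the surveillance interval.

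**4. Can a six-month lag matter for classification?** The printed coefficients are 0.09 for age in years, 2.34 for log AFP and 1.33 for log DCP. The log base is not stated, so both are shown. The marker rises are assumptions, not figures from the document.

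| Change over six months | Shift in score, log10 | Shift in score, natural log |
|---|---|---|
| Age alone: 0.09 × 0.5 | 0.045 | 0.045 |
| AFP × 1.5: 2.34 × log 1.5 | 0.41 | 0.95 |
| AFP × 2: 2.34 × log 2 | 0.70 | 1.62 |
| DCP × 2: 1.33 × log 2 | 0.40 | 0.92 |

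Ageing alone is negligible. A real change in a marker could move a score near the cut-off of -0.63 from one side to the other.

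**5. Which analyses can this reach?**
- *Baseline specificity: yes.* Every enrolled participant has a negative enrolment MRI, so each baseline score counts as a true negative or a false positive.
- *Sensitivity for incident HCC: no.* The baseline pair contains no cases.
- *Time-varying Cox model: yes, at the start.* Time to event runs from entry, so the entry score is the first covariate value. If the value is updated at each visit, it is replaced at month 6.
- *Share of scores.* Ten visits for 1,600 participants give 16,000 scheduled scores. If every entry score were old, 1,600 / 16,000 = 10% would be affected. This is a ceiling, not an estimate.

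**The case against.** The strongest reply is the list's opening sentence, which describes tests that each participant has upon entry and places GALAD beside the MRI. The most recent visit within six months can also be read as including Visit 1. On that reading six months is only an outer limit, and most scores would fall inside the 30-day screening and enrolment period. This stands in part. A reader might infer that the plan uses old results in place of Visit 1 blood, but the text does not say that. It permits old results and does not require fresh ones.

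Other stronger readings also lack support:
- **Contradiction with the four-week window under Outcome ascertainment.** That window concerns a visit at which an indication arose during surveillance. It does not govern the gap between GALAD and MRI at entry.
- **Entry markers mostly missing, or from mixed laboratories.** The Discussion describes national practice. It does not say what the study sites can run or how many eligible patients have prior results. Where no prior result exists, no old score can be used, so scarcity lowers the number affected.
- **Selective testing in both countries.** The indications for testing are described for Vietnam only.
- **Vitamin K exposure cannot be checked for an earlier draw.** The seven-day criterion is tied to the clinic visit, but medication history is taken at enrolment. The documents do not show that earlier exposure is unknowable.
- **Bias in the primary sensitivity measure.** The negative enrolment MRI rules this out for the baseline pair.

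What the reply does not remove is the difference between the MELD and GALAD items, or the fact that a six-month-old score complies with the rule.

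**Conclusion.** The point holds in a limited form. The GALAD line permits an entry score up to about 26 weeks older than the enrolment MRI, and it omits the entry alternative given for MELD. In Vietnam, any earlier results may come selectively from patients under suspicion. The selection is inferred from the described local use and is not documented for the study cohort.

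The effect is confined to baseline specificity and the Cox starting value, at most one of ten scores per participant. The number affected is unknown, and the documents do not settle the direction or size of any bias. It is still worth correcting, because the mismatch is avoidable with blood that is already being drawn.

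**What to change.** Reword the GALAD item in Variables assessments and definition along these lines: the entry GALAD score is calculated from AFP, AFP-L3 and DCP measured on blood drawn at screening/Visit 1, within the same screening and enrolment period (up to 30 days, as in the Figure 3 caption) as the enrolment MRI; results from before that period are recorded as descriptive history and are not used in the performance analysis.

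It should be stated explicitly that the MRI falls within that period, since the caption speaks of procedures in general.

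The change is one sentence and needs no new blood draw. The cost is one extra assay set (AFP, AFP-L3 and DCP) for each participant who would otherwise have reused an old result.

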### Outcome ascertainment and study exit definitions

Time of positive surveillance: latest date of visit with lab resultsCriteria for outcome assessment: elevated GALAD score and/or suspicion of liver tumor on ultrasound, whichever comes firstDate of detection of liver tumor ≥ 1 cm in size on dynamic contrast-enhanced MRI or confirmation of HCC on biopsyOutcome captured if multiphase MRI with contrast is not needed when GALAD score is less than the cut-off and ultrasound findings are normal.Tumor of any size and quantity will be recorded.Person-years of follow-up time: calculated for each participant from one year after the enrollment date to the event date (indication for multiphase MRI with contrast; HCC diagnosis; date of loss to follow-up, or end of study, whichever comes first).Time to event: from entry in the study to the date of liver tumor detection on multiphase MRI with contrast or on the date of biopsy with HCC confirmation.GALAD score and ultrasound: within four weeks of the visit with indicationLoss to follow-up: 12 months of last clinic encounter with no study visitsEnd of study: completion of the last visit or procedure shown in Table 1 or when a patient develops HCC and then subject to the local management protocol (above)

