### Study schedule and assessments

Figure 2 depicts the study schema. The study is planned for five years. Individuals with a liver mass ≥ 1 cm in diameter, elevated AFP (≥ 9 ng/mL), and/or elevated GALAD score (≥ -0.63) will be scanned with dynamic contrast-enhanced MRI, and a diagnosis of HCC will be made by LiRADS-5. Additionally, those who do not exhibit abnormal imaging findings, elevated AFP titer, and/or elevated GALAD score will obtain a dynamic contrast-enhanced MRI annually for five years to assess for HCC. In Vietnam, the study sites and the funds to be received for the study will be used for conducting all the tests and MRIs. National health insurance will not be used. In Saudi Arabia, national health insurance will cover the participants’ tests and MRIs.

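### Person-years and time to event run on different clocks, and person-years stop at the positive test that prompts the MRI, so any incidence rate built on them would be biased

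*Protocol article*

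**What the plan says.** Both definitions stand in the Protocol article under Outcome ascertainment and study exit definitions.

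- **Person-years** are "calculated for each participant from one year after the enrollment date to the event date (indication for multiphase MRI with contrast; HCC diagnosis", followed by "date of loss to follow-up, or end of study, whichever comes first".
- **Time to event** runs "from entry in the study to the date of liver tumor detection on multiphase MRI with contrast or on the date of biopsy with HCC" confirmation.

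Three other statements bear on these definitions.

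- **What indicates an MRI** (Study schedule and assessments): besides a liver mass of at least 1 cm, participants with "elevated AFP (≥ 9 ng/mL), and/or elevated GALAD score (≥ -0.63) will be scanned with dynamic contrast-enhanced MRI". Those with no trigger are also imaged: participants without abnormal imaging, raised AFP and/or "elevated GALAD score will obtain a dynamic contrast-enhanced MRI annually for five years to assess for HCC".
- **Baseline exclusion** (Screening): "All patients will be required to have a negative dynamic contrast-enhanced MRI upon study enrollment to rule out HCC before the study enrollment".
- **Expected cases** (text after Fig. 2): 80 at 1% a year to 320 at 4% a year, over five years in the whole cohort.

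**The concern.** **Origin.** A cancer found at the 6-month visit is an event on the time-to-event clock, but it falls half a year before person-time opens. One found at month 12 has zero person-time. No reason is given for the delay. A washout for prevalent disease is the natural explanation, but the baseline MRI already serves that purpose and the time-to-event definition applies no washout.

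**End.** The MRI indication is the positive surveillance result. For a test-detected cancer, person-time closes at that result, which is at or before the diagnosis. For a participant without cancer it closes at the first false positive, although that person stays in the study and continues to have annual MRI. Observed follow-up is thus discarded according to the value of the marker being evaluated.

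**At stake.** Any incidence rate that uses these person-years is affected. The Cox model could be affected too: the time-to-event definition gives an end date only for cases. The one list of end dates that covers participants without HCC sits in the person-years definition, next to the MRI indication.

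**Working it through.** **1. Reproduce the plan's figures.** Expected cases = N × annual incidence × years: 1,600 × 0.01 × 5 = 80 and 1,600 × 0.04 × 5 = 320. Both match, and both count from enrolment over five years. With full follow-up, person-time from enrolment is 1,600 × 5 = 8,000 person-years (PY), giving 80/8,000 = 1.0 and 320/8,000 = 4.0 per 100 PY.

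**2. One-year delay alone, ignoring attrition and the MRI stop.** The second row takes the last listed follow-up visit, 54 months (Follow-up visits), as the end. Year 1 is expected to hold 1,600 × 0.01 = 16 or 1,600 × 0.04 = 64 cases.

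| Follow-up | PY after month 12 | All cases in numerator, per 100 PY | Year-1 cases dropped, per 100 PY |
|---|---|---|---|
| 5 years | 1,600 × 4 = 6,400 | 80/6,400 = 1.25; 320/6,400 = 5.0 | 64/6,400 = 1.0; 256/6,400 = 4.0 |
| 4.5 years | 1,600 × 3.5 = 5,600 | 72/5,600 = 1.29; 288/5,600 = 5.14 | 56/5,600 = 1.0; 224/5,600 = 4.0 |

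If year-1 cases are counted, the overstatement is 5/4 = 1.25 (+25%) or 4.5/3.5 = 1.286 (+29%). If they are dropped with their person-time, the delay causes no bias. The document does not say which applies.

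**3. Stop at a false positive.** Let q be the chance that a visit by an HCC-free participant triggers an MRI. The documents do not give q; 5–20% is assumed. With nine follow-up visits treated as independent, the share stopped at least once is 1 − (1 − q)^9: 37% at q = 0.05, 61% at 0.10 and 87% at 0.20. Positivity that persists within a person lowers these shares, so they are upper-end illustrations.

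**4. Delay and stop together.** This is an illustrative simulation with assumptions that are not in the documents: 54 months of visits, 70% per-visit sensitivity of the combined triggers, one month from indication to diagnosis, q from 0 to 20%, no loss to follow-up.

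| True incidence, per 100 PY | All HCC over the plan's PY | Only HCC diagnosed inside the window |
|---|---|---|
| 1.0 | 1.3 (q = 0) to 3.6 (q = 0.20) | about 0.2 |
| 4.0 | 5.2 (q = 0) to 14.0 (q = 0.20) | 0.7 to 0.8 |

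At 1% incidence, the plan's person-years fall from 5,465 (q = 0) to 1,981 (q = 0.20), against about 7,070 from entry to diagnosis. The share of cancers diagnosed inside the window falls from 16% to 5%. The last column is the extreme of that reading, because every triggered diagnosis is dated one month after its trigger, even when a scheduled MRI falls at the same visit.

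**5. What does not depend on the rule.** The expected cases use N, annual incidence and five years. The sample sizes of 621 and 119 rest on five-year proportions. Sensitivity and false-positive results are counts against the MRI reference. None of these uses person-years.

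**The case against.** The strongest reply is that no named analysis uses person-years. The term appears once. Statistical methods lists bootstrap, Cox, and GEE or mixed models, with no incidence-rate estimator, and the primary endpoint is GALAD performance at the −0.63 cut-off. This stands, and it limits the importance of the point.

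A reader might infer that the study's incidence is simply wrong. The documents do not support that: they never pair a numerator with these person-years, and a delayed start that also drops year-1 events gives the planning rates back.

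A reader might also infer that every test-detected cancer falls outside the person-time and that only cancers missed by the tests can end it as a diagnosis. That is too strong. Table 1 schedules contrast imaging at Visits 3, 5, 7 and 10 alongside ultrasound and blood collection, so trigger and MRI can coincide. Safety reporting foresees masses found outside the study. If a case is dated at the indication that led to it, it sits on the boundary and can be counted.

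That last reading does not rescue the rule. It makes a positive test the event, so false positives either count as events or are censored because of the marker. Cancers found after an earlier false positive are still lost.

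Finally, the Cox model is for time to HCC, which has its own definition with neither the delay nor the stop. Under that definition it is unaffected. What remains is that this definition names no censoring date for participants without HCC, so the person-years list could be borrowed. In the time-varying biomarker model described in the abstract, nobody would then accrue time at risk after first reaching −0.63.

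**Conclusion.** The point holds as an inconsistency within one section, plus an end date that should not be there. Stopping time at risk at a positive test is wrong on every reading: it either changes the endpoint to a positive test or cuts follow-up short on the marker under evaluation.

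The size is conditional. The 25–29% excess is exact arithmetic, but it applies only if year-1 cases stay in the numerator. The MRI-indication stop can move a rate several-fold in either direction, but that rests on assumed trigger rates, sensitivity and timing.

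It would be tempting to conclude that the hazard analyses and the main results are biased and that the study cannot proceed without a correction. The documents do not support this: the primary estimates and the sample size are untouched, and the Cox analysis is affected only if it borrows the person-years end dates. The point should be fixed before analysis; it is not a critical defect.

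**What to change.** Reword the section on outcome ascertainment and study exit definitions, and carry the same wording into the analysis plan:

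1. Use one origin for both quantities: enrolment, after the negative baseline MRI.
2. Use one end for both: HCC diagnosis, else death, loss to follow-up or end of study. Death is not in the present list.
3. Remove the MRI indication as an end date. Record it as an intermediate date and treat it as a time-varying surveillance result.
4. If a one-year landmark is wanted, label it a sensitivity analysis and restrict events and person-time alike.

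The cost is wording only. Enrolment, surveillance, MRI and diagnosis dates are already collected, and neither the visit schedule nor the sample size changes.

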## Methods / design

### Objectives

The primary objective of the study is to prospectively evaluate the performance of GALAD score as a biomarker-based surveillance model to detect early HCC in patients with advanced fibrosis or cirrhosis (e.g., Metavir F3 or higher, with model for end-stage liver disease [MELD] 15 or lower). The secondary objective is to collect and archive biospecimens to develop a bio-repository for future studies in chronic liver diseases.

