### Outcome measures

The primary endpoint is the performance of GALAD score determined in association with HCC detection by LiRADS criteria in a cohort with advanced fibrosis or cirrhosis (e.g., Metavir F3 or higher, with MELD 15 or lower) undergoing prospective surveillance every six months for five years. Performance of GALAD score will be determined by using the GALAD score cut-off value of -0.63 to prospectively survey a cohort of 1,600 patients with advanced fibrosis and early cirrhosis (e.g., Metavir F3 or higher, with MELD 15 or lower) for early detection of HCC by Liver Imaging Reporting and Data System (LiRADS) assessment (LiRADS-5). The GALAD cut-off value was previously determined in case–control studies [11]. For the establishment of the biorepository, the endpoint is the proportion of study participants who agree to consent for bio-specimen when invited.

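### The HCC event is LiRADS-5 in the primary endpoint, but any liver tumour on MRI, or biopsy-confirmed HCC, in the time-to-event rule

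*Protocol article*

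**What the plan says.** Under Outcome measures the article states: "The primary endpoint is the performance of GALAD score determined in association with HCC detection by LiRADS criteria". The same paragraph names LiRADS-5 as the category. Study schedule and assessments agrees that "a diagnosis of HCC will be made by LiRADS-5", and so do the Abstract and the Fig. 2 legend. None of these lists biopsy as a route to being a case.

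Outcome ascertainment and study exit definitions is worded differently:

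- Time to event runs from entry "to the date of liver tumor detection on multiphase MRI with contrast or on the date of biopsy with HCC confirmation". It gives no LiRADS category and no size.
- Another line in that section dates detection of a tumour of at least 1 cm on MRI, or biopsy confirmation of HCC. Again there is no LiRADS category.
- A further line says "Tumor of any size and quantity will be recorded".
- Person-years stop at the earliest of: "indication for multiphase MRI with contrast; HCC diagnosis; date of loss to follow-up, or end of study, whichever comes first".

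The Abstract calls the Cox outcome time to HCC.

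On stage, the primary objective is "to prospectively evaluate the performance of GALAD score as a biomarker-based surveillance model to detect early HCC", and the text following Fig. 2 names sensitivity for early HCC as the primary outcome measure. The endpoint under Outcome measures carries no stage, size or number limit.

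**The concern.** An accuracy analysis and a time-to-event analysis of the same cohort should share one set of cases. Here a participant can be a case in one and not in the other.

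The article itself expects participants in that gap. Safety reporting anticipates inconclusive nodules on imaging and biopsy. The Discussion describes nodules without the typical enhancement pattern. Enrollment and Follow-up visits both provide for liver biopsy.

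At stake are the hazard ratios for GALAD, which would be estimated partly on lesions that are not HCC, and the two-by-two table behind sensitivity and false-positive results, which would place some proven cancers among the non-cases.

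**Working it through.** **1. The definitions side by side.** The first data column is the LiRADS-5 definition (Abstract, Outcome measures, Study schedule and assessments). The second is the time-to-event line.

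| Finding in a participant | LiRADS-5 definition | Time-to-event line |
|---|---|---|
| LiRADS-5 lesion on MRI | case | event |
| Tumour on MRI, not LiRADS-5, no biopsy proof of HCC | non-case | event |
| Biopsy-proven HCC, not LiRADS-5 | non-case | event |
| No tumour | non-case | no event |

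The two middle rows disagree. The second puts non-HCC lesions into the Cox analysis. The third puts a proven HCC among the non-cases of the accuracy analysis: a false positive if GALAD ≥ -0.63, a true negative if below.

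**2. The plan's own counts.** Expected cases are participants × annual incidence × years: 1,600 × 0.01 × 5 = 80 and 1,600 × 0.04 × 5 = 320. Both match the text following Fig. 2.

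The Sample size figures also reproduce. The inputs are two-sided alpha 0.05, 90% power, two proportions with continuity correction, and a doubling of the 5-year proportion. The doubling is inferred, because the comparator is not stated. 0.05 against 0.10 gives 621, and 0.20 against 0.40 gives 119. These rest on all-HCC incidence and do not use the time-to-event line.

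**3. Possible size of the mismatch in the Cox analysis.** Let L be the number of participants whose counted lesion is not HCC, and C the true HCC cases. The non-HCC share of events is L / (L + C). The document gives no L. Assume 3–10% of 1,600, that is 48 to 160.

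| | C = 80 | C = 320 |
|---|---|---|
| L = 48 | 48/128 = 38% | 48/368 = 13% |
| L = 160 | 160/240 = 67% | 160/480 = 33% |

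The range over the document's own case counts is 13–67%. It assumes that every such lesion is called a tumour and that none of these participants also has HCC. A lesion that biopsy proves to be HCC leaves L. Loss to follow-up that falls equally on L and C leaves the share unchanged.

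**4. Precision if the estimate is restricted to early HCC.** The half-width of a 95% interval is 1.96 × √(0.7 × 0.3 / n), at an assumed sensitivity of 70%. The early share is also an assumption, 60–80%.

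- Of 80 cases, 48 to 64 are early: ±13.0 to ±11.2 points, against ±10.0 with all 80.
- Of 320 cases, 192 to 256 are early: ±6.5 to ±5.6 points, against ±5.0 with all 320.

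**The case against.** The best reply is that the time-to-event line only dates a case and does not define one. Diagnosis is set elsewhere as LiRADS-5, the Abstract speaks of time to HCC, and the outcome section itself lists HCC diagnosis among the person-years endpoints and ends participation when HCC develops. That may well be what was meant. But the text does not say so, and the reading does not explain the biopsy route, which reaches beyond LiRADS-5. A tumour of at least 1 cm in one line and of unstated size in another adds to the ambiguity.

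Other parts of the reply stand, and they rule out stronger readings that a reader might infer:

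- That the study cannot answer an early-detection question. Sensitivity for early HCC is already named as the primary outcome measure, and tumour size and number are recorded, so an early subset can be derived. A detailed criterion for early disease may sit in the full protocol, which is not shown.
- That non-HCC lesions become GALAD misses in the accuracy analysis. They cannot, because that analysis uses LiRADS-5.
- That most time-to-event events would certainly be false. The 38–67% range holds only at 80 cases; at 320 it is 13–33%.
- That the sample size is wrong. It reproduces and does not depend on this point.

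**Conclusion.** The contradiction is in the text and needs reconciling: the two analyses, followed as written, have different cases. The effect on the Cox analysis could be modest or large, 13–67% of events under an assumed 3–10% lesion rate and the document's 80–320 cases. The number of biopsy-proven HCCs that are not LiRADS-5 cannot be estimated from the document.

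The missing criterion for early disease is a lesser matter. It is a misalignment between the endpoint as worded and the objective, not evidence that the objective is out of reach. It should still be settled before GALAD results are analysed, because a cut-off chosen afterwards would weaken a prospective validation.

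**What to change.** Use one analysis case definition in the Abstract, Outcome measures, Study schedule and assessments, and Outcome ascertainment and study exit definitions: LiRADS-5 or biopsy-confirmed HCC, dated at the first MRI or biopsy that meets it. For analysis, a lesion that does not meet it leaves the participant event-free. Reconcile the person-years line with the same definition. This is a rule for counting events and leaves patient work-up as it is.

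Align the endpoint under Outcome measures with the Objectives by fixing a criterion for early HCC from the recorded tumour size and number, before GALAD results are analysed. The choice of staging cut-off is the sponsor's.

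The cost is mainly wording, since biopsy results, tumour size and tumour number are already collected. The price is precision: the early-HCC sensitivity estimate rests on fewer cases, as shown above. The stated 621 and 119 need no change for this point. If the sponsor chose to size the study on early HCC as well, keeping the inferred doubling at 1% per year, the requirement would rise from 621 to 788 per group at an assumed 80% early share and to 1,068 at 60%.
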